**Categories for Determining Relationship to Trial Drug:**

**PROBABLE** (must have first three)

This category applies to those adverse events which are considered, with a high degree of certainty, to be related to the test drug. An adverse event may be considered **probable**, if:

1. It follows a reasonable temporal sequence from administration of the drug.

2. It cannot be reasonably explained by the known characteristics of the subject's clinical state, environmental or toxic factors, or other modes of therapy administered to the subject.

3. It disappears or decreases on cessation or reduction in dose. (There are important exceptions when an adverse event does not disappear upon discontinuation of the drug, yet drug-relatedness clearly exists; eg. [1] bone marrow depression, [2] tardive dyskinesias.)

4. It follows a known pattern of response to the suspected drug.

5. It reappears upon re-challenge.

**POSSIBLE** (must have the first two)

This category applies to those adverse events in which the connection with the test drug administration appears unlikely, but cannot be ruled out with certainty. An adverse event may be considered **possible** if, or when:

1. It follows a reasonable temporal sequence from administration of the drug.

2. It may have been produced by the subject's clinical state, environmental or toxic factors, or other modes of therapy administered to the subject.

3. It follows a known pattern of response to the suspected drug.

**REMOTE** (must have the first two)

In general, this category is applicable to an adverse event which meets the following criteria:

1. It does **not** follow a reasonable temporal sequence from administration of the drug.

2. It may readily have been produced by the subject's clinical state, environmental or toxic factors, or other modes of therapy administered to the subject.

3. It does not follow a known pattern of response to the suspected drug.

4. It does not reappear or worsen when the drug is re-administered.

**UNRELATED**

This category is applicable to those adverse events which are judged to be clearly and incontrovertibly due only to extraneous causes (disease, environment, etc.) and do not meet the criteria for drug relationship listed under REMOTE, POSSIBLE or PROBABLE.

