**10 STATISTICAL STATEMENT**

**10.1 Statistical Hypothesis**

Study hypotheses:

i) Cure rate of resistant malaria after Cotrifazid treatment is not inferior to the one obtained after treatment with mefloquine or quinine and Fansidar.

ii) Cotrifazid is safe to use in semi-immune patients with resistant malaria. No IRAE attributable to the drug is expected in the subjects.

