**10.4.2 Primary Safety Parameters**

Rates of acute and subacute AEs by severity and relation to the drug will be compared between the Cotrifazid and the comparator groups. Laboratory parameters (haematological) in the two groups will be compared.

The Mantel-Haenzel Chi-square test (x2=0.05, two-tailed) will be used to assess any significant difference between the two groups in terms of number of AEs reported.

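### In Section 5.2.2 the listed criteria for POSSIBLE and REMOTE shut disease-caused events out of UNRELATED and contradict the sentence introducing POSSIBLE, so causality coding depends on how the scale is read

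*Protocol*

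**What the plan says.** Section 5.2.2 of the protocol gives the investigator a four-level causality scale. POSSIBLE and REMOTE each carry the rule "must have the first two".

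- **POSSIBLE**: item 1 is a reasonable temporal sequence. Item 2 reads "It may have been produced by the subject's clinical state, environmental or toxic factors", or by other therapy. A sentence ahead of the list confines the category to events whose link to the drug seems unlikely but cannot be excluded for certain.
- **REMOTE**: item 1 is the absence of a reasonable temporal sequence. Item 2 reads "It may readily have been produced by the subject's clinical state, environmental or toxic factors", or by other therapy. No sentence limits it to cases where the drug remains in question.
- **UNRELATED**: two conditions joined by a conjunction. It covers events judged beyond dispute to be "due only to extraneous causes (disease, environment, etc.) and do not meet the criteria for drug relationship listed under REMOTE, POSSIBLE or PROBABLE".

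The codes are used in two places. Section 10.4.2 says "Rates of acute and subacute AEs by severity and relation to the drug will be compared" between the groups, under primary safety parameters. Section 10.1(ii) says "No IRAE attributable to the drug is expected in the subjects". Neither section says which levels count as drug-related or attributable.

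**The concern.** A competing cause would normally count against a drug relationship. Here it is a required item for two of the three drug-relationship levels, and meeting either level disqualifies the event from UNRELATED. Every patient in this trial has malaria, so new or worsening disease events can be expected in all arms, and they are the events that UNRELATED seems meant to hold.

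If two investigators, or the two centres, resolve the conflict differently, the same malaria event is POSSIBLE in one set of records and UNRELATED in another. The by-relation rates then partly reflect the reading of the scale. A serious malaria complication during dosing could be classed as possibly drug-related by the list alone, which bears on hypothesis (ii). The investigator assigns the code at the time, so a later analysis plan can regroup levels but cannot separate disease events from genuine possible reactions within one level.

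**Working it through.** The plan gives no figure to reproduce on this point. The check is an enumeration of the scale's own rules.

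**Inputs (all from Section 5.2.2).**
- T: reasonable temporal sequence, yes or no.
- X: another cause may have produced the event, yes or no.
- D: improves on stopping or dose reduction (item 3 of PROBABLE), yes or no.
- R: incontrovertibly due only to extraneous causes. R implies X.

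**Rules from the numbered items.**
- PROBABLE = T and not X and D
- POSSIBLE = T and X
- REMOTE = not T and X
- UNRELATED = R and none of the above

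Under reading (b), the introductory sentence changes POSSIBLE to T and X and not R, because an event certainly due to something else has had the drug link excluded.

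**Result for the four combinations with R true.**

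| T | D | (a) Listed items alone | (b) With the sentence introducing POSSIBLE |
|---|---|---|---|
| yes | yes | POSSIBLE | UNRELATED |
| yes | no | POSSIBLE | UNRELATED |
| no | yes | REMOTE | REMOTE |
| no | no | REMOTE | REMOTE |

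Reading (a) returns UNRELATED in 0 of 4 and reading (b) in 2 of 4. Reading (b) also inverts the scale. A certainly malarial event with plausible timing is UNRELATED. The same event without plausible timing, for which the case against the drug is stronger, is REMOTE.

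**Which analyses are exposed.** The test named in 10.4.2 is applied to the number of adverse events reported, with no causality filter, and the synopsis also compares the rate and type of all adverse events. Causality coding cannot change these. It can change the by-relation rates and the count behind 10.1(ii). Only changes from baseline are adverse events under 5.2.2, so unchanged presenting symptoms do not enter.

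**Illustration of dilution.** The protocol gives no adverse event rates, so these are assumptions: truly drug-caused events in d = 10% v 25% of patients, 110 per arm (Section 10.3), two-sided 5%, and an equal, independent malaria background m in both arms, all counted as drug-related. The risk per arm is p = 1 − (1 − d)(1 − m). Power is Φ[(|p1 − p2| − 1.96·SE0)/SE1], with SE0 pooled and SE1 unpooled.

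For m = 0.20: p1 = 1 − 0.90 × 0.80 = 0.28, p2 = 1 − 0.75 × 0.80 = 0.40, and the ratio is 0.40/0.28 = 1.43.

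| m | p1 | p2 | Risk ratio | Power |
|---|---|---|---|---|
| 0 | 0.100 | 0.250 | 2.50 | 0.84 |
| 0.10 | 0.190 | 0.325 | 1.71 | 0.63 |
| 0.20 | 0.280 | 0.400 | 1.43 | 0.47 |
| 0.30 | 0.370 | 0.475 | 1.28 | 0.35 |
| 0.40 | 0.460 | 0.550 | 1.20 | 0.27 |
| 0.50 | 0.550 | 0.625 | 1.14 | 0.20 |

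The table contrasts perfect attribution (m = 0) with every background event being counted as related. It also supposes a pooled drug-related class, which the protocol does not define.

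**The case against.** The strongest reply is that the scale, read whole, works. The sentence introducing POSSIBLE and the first half of UNRELATED are near complements: if the drug can be excluded, the event is UNRELATED, and if it cannot, POSSIBLE is the right code. The required items are a minimum and not a command, since the wording around POSSIBLE and REMOTE is permissive. No analysis pools POSSIBLE with PROBABLE, the named test uses all events, and the power figures rest on assumed rates and an extreme contrast. Hypothesis (ii) states an expectation with no test attached, and it does not equate attributable with POSSIBLE.

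Much of this stands. A reader might infer from the listed items that UNRELATED can never be used. The documents do not support that, because the introductory sentence and the permissive wording let an investigator keep a plainly malarial event out of POSSIBLE. Nor do they show that the safety comparison will lose the power tabulated above, or that a malaria complication would refute hypothesis (ii).

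What the reply does not remove is the conflict itself. The UNRELATED clause refers to the criteria listed under the other levels, and the listed criteria catch every disease-caused event. Nothing says that the introductory sentence overrides them. REMOTE has no such sentence, so its overlap with UNRELATED remains on either reading.

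**Conclusion.** The point holds as an internal contradiction in 5.2.2. On the listed criteria, a certainly extraneous event is always POSSIBLE or REMOTE. With the sentence introducing POSSIBLE, it is UNRELATED if temporally associated and REMOTE if not. The practical effect is that new or worsened malaria events during dosing can be coded in either of two ways, so the by-relation rates in 10.4.2 and the count of attributable IRAEs in 10.1(ii) are not reliably defined.

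The all-event chi-square test is untouched. The protocol fixes no size for the effect. A fall in power from 0.84 to between 0.63 and 0.20 is what the assumed rates give if all background events are coded POSSIBLE and POSSIBLE is counted as related; it is not a forecast. The correction is worth making before enrolment because miscoded events cannot be sorted out from the codes afterwards.

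**What to change.** 1. Apply UNRELATED first. Delete the clause requiring that events "do not meet the criteria for drug relationship listed under REMOTE, POSSIBLE or PROBABLE", and state that an event judged clearly due to malaria or another non-drug cause is UNRELATED whatever its timing.
2. Reword item 2 of POSSIBLE to say that another cause is possible but does not clearly account for the event, and align item 2 of REMOTE with it.
3. State which levels count as attributable in 10.1(ii) and as drug-related in 10.4.2. For the by-relation rates this could sit in the analysis plan; the wording of the scale itself cannot.

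With steps 1 and 2, all four combinations with R true go to UNRELATED. Events with another possible but not certain cause go to POSSIBLE or REMOTE by timing.

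The cost is a change to the wording of 5.2.2 and to the matching case report form instruction, with no new data. The downside is that investigators, who know the allocation (Section 4.2), gain discretion to dismiss an event as UNRELATED. The comparison of all adverse events, already planned, guards against that and should be kept beside the by-relation results.

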**5.2.3 Immediately Reportable Adverse Events**

Any adverse event that is considered SERIOUS (as defined below) must be reported IMMEDIATELY by the investigator, ie. within one working day of becoming aware of the event.

An **Immediately Reportable Adverse Event (IRAE)** is any serious adverse event or abnormal laboratory test value that occurs during the defined treatment period, and which suggests a significant hazard, contraindication, side effect or precaution. An IRAE **must** be immediately reported to the clinical monitors **within one working day**.

***Immediately Reportable adverse events*** include any event or experience that is:

- fatal;

- life threatening;

- permanently disabling (ie. severely incapacitating or interfering with the ability to resume usual life patterns);

- requires inpatient hospitalisation or prolonged hospitalisation;

- an overdose (ie. a deliberate or inadvertent administration of a treatment at a dose higher than that specified in the protocol *and* higher than known therapeutic doses for that specific indication);

The definition of an IRAE includes any event which is expected or unexpected, related or unrelated to the drug.

All IRAEs must also be reported on the adverse events page of the CRF and must be assessed for severity and the relationship to the trial medication. The actions taken by the investigator and the outcome of the event must be reported.

**IRAEs must be reported to the appropriate ethics committee, if requested by the committee and/or according to local legal requirements.**

It is important that the SEVERITY of an adverse event is not confused with the SERIOUSNESS of the event. For example, vomiting which persists for many hours may be severe, but is not necessarily a serious adverse event. On the other hand, stroke which results in only a limited degree of disability may be considered a mild stroke, but would be a serious adverse event.

**5.2.4 Drug Administration and Follow-Up of Adverse Events**

All adverse events MUST be documented and followed up until the event is either resolved or adequately explained, even after the subject has completed their trial treatment.

**5.3 Assessment of Efficacy**

**5.3.1 Primary Efficacy Parameters**

The primary parameters of efficacy i) fever clearance time, ii) parasite clearance time, iii) failure rate, iv) occurrence of complications, information collected from day 1,2,3, 7 and 14.

Thick and thin blood films will be Giemsa stained and species-specific density will be counted per/200 white blood cells (WBC). Slides will be declared negative if no parasites are seen in 100 thick film fields. Parasite density per microliter blood will be calculated by multiplying the parasitemia/200 WBC by a WBC count of 10000/L in children aged < 5 years and of 8000/L in persons aged > 5 years.

1. **Secondary Efficacy Parameters**

The secondary parameters of efficacy are i) symptom clearance time, information collected at day 1,2,3, 7 and 14, and ii) haemoglobin concentration from samples collected at day 14.

1. **Assessment of Pharmacology**

Pharmacokinetics will be assessed in a small subsample of patients (5). Blood will be drawn (2 ml by venepuncture) at hour 2, 8, 16, 24, 36, 72.

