**1.2 Objectives of the Trial**

The purpose of this trial is to assess the efficacy and safety (primary parameters) of Cotrifazid in semi-immune Papua New Guinean patients with resistant malaria.

More specifically i) to compare the efficacy of Cotrifazid versus Lariam (mefloquine) or standard treatment in semi-immune subjects with resistant malaria, and ii) to compare the tolerance of Cotrifazid versus Lariam or standard treatment in semi-immune subjects with resistant malaria.

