**10.2 Study Design**

This is a multicentric, open, block-randomised, comparative study.

1. **Sample Size Calculation**

The overall sample size of 330 (110 in Cotrifazid group, 110 in Lariam group and 110 in standard treatment group) is sufficient to demonstrate that Cotrifazid is not inferior to Lariam or quinine and Fansidar, assuming a rate of treatment success of 95% with Lariam or quinine and Fansidar and a clinically acceptable rate of treatment success of 86% or more in the Cotrifazid group, a 10% loss of follow-up (80% power, 95% confidence limits, one-sided test) (formula from Jones et al, 1996).

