**10.4 Strategy for Statistical Analysis**

**10.4.1 Efficacy Parameters**

**10.4.1.1 Primary Efficacy Parameters**

Efficacy will be estimated by comparing the rate of treatment failure, and proportions of complications between the Cotrifazid and comparator groups, using the Mantel-Haenzel Chi-square test (x2=0.05, one-tailed). The time to fever clearance and the time to parasite clearance will also be compared between the Cotrifazid and comparator groups. Survival curves showing the clearance time will be plotted for the two groups, and compared using the logrank test.

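### One efficacy outcome is hypothesised and sized, but four unranked outcomes are called primary, and the rule for the two comparators is left open

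*Protocol*

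**What the plan says.** **Hypothesis and sample size: one outcome.** Section 10.1 gives a single efficacy hypothesis: "Cure rate of resistant malaria after Cotrifazid treatment is not inferior to the one obtained after treatment with mefloquine or quinine and Fansidar". Section 10.3 assumes 95% treatment success on either comparator and accepts 86% or more on Cotrifazid, one-sided. Its arms are "110 in Cotrifazid group, 110 in Lariam group and 110 in standard treatment group".

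**Endpoint sections: four outcomes.** Section 5.3.1 reads "The primary parameters of efficacy i) fever clearance time, ii) parasite clearance time, iii) failure rate, iv) occurrence of complications", with no order. The synopsis lists the same four, and 10.4.1.1 analyses all four under its primary heading.

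**Comparators.** Section 1.2 sets out "to compare the efficacy of Cotrifazid versus Lariam (mefloquine) or standard treatment in semi-immune subjects with resistant malaria". The same or recurs in 10.1 and 10.3.

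**Tests.** For two outcomes, 10.4.1.1 plans "comparing the rate of treatment failure, and proportions of complications between the Cotrifazid and comparator groups", "using the Mantel-Haenzel Chi-square test (x2=0.05, one-tailed"). For the two clearance times it says "Survival curves showing the clearance time will be plotted for the two groups, and compared using the logrank test", with no significance level or sidedness. The two-group wording returns for symptom clearance and haemoglobin in 10.4.1.2, and in 10.4.2, which looks for "any significant difference between the two groups in terms of number of AEs reported".

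**The concern.** A three-arm trial with two active comparators needs two things fixed before data are seen: the outcome on which efficacy is judged, and whether Cotrifazid must match one comparator or both. Sections 10.1 and 10.3 answer the first with cure rate, but 5.3.1 and 10.4.1.1 put three further outcomes on the same level. A margin exists only for treatment success, so for the other three the protocol does not say what result would count in favour of Cotrifazid. The second question has no explicit answer, and a test for two groups cannot be applied to three arms without choosing a pair or merging two arms.

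The same data could therefore support different conclusions. The trial is open-label (4.2), so those who settle the reading later may already know how the arms compare.

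**Working it through.** **Inputs.** From the protocol: success 95% on the comparators, lowest acceptable Cotrifazid success 86%, hence a margin of 95 − 86 = 9 points; one-sided 5%; 80% power; 10% loss; 110 per arm, hence 110 × 0.9 = 99 evaluable. Assumed: the correlation between the four outcomes (0 to 0.8), 5% one-sided for the logrank tests, and the rates in the pooling example.

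**1. The planned sample size.** n per arm = 2p(1 − p)(z₁₋α + z_power)² / δ², with p = 0.95 and δ = 0.09.
- As stated (5% one-sided, 80% power): 0.095 × (1.645 + 0.842)² / 0.0081 = 72.5, so 73. Divided by 0.9, this is 82 per arm.
- With z = 1.282 in place of 0.842 (90% power, or the equivalence form with half of beta): 100.4, and 100.4 × 1.1 = 110.5, close to the planned 110.

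So 110 per arm is more than the stated inputs require, and it is derived from treatment success only.

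**2. Error on the efficacy claim under each reading.** Cotrifazid is shared by both comparisons, so for a given outcome the two test statistics have correlation 0.5.

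| Reading | Chance of a false claim |
|---|---|
| Treatment success, both comparators required | at most 5% |
| Treatment success, either comparator suffices | 8.8% (if independent, 1 − 0.95² = 9.75%) |
| Any of four outcomes, either comparator, outcome correlation 0 | 30.8% (if independent, 1 − 0.95⁸ = 33.7%) |
| Same, correlation 0.5 | 23.9% |
| Same, correlation 0.8 | 17.8% |

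The first row needs no simulation. If Cotrifazid is inferior to at least one comparator, the chance of passing both tests cannot exceed the chance of passing that one, which is 5%. The other rows are simulations with every null hypothesis true at its boundary.

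**3. What the comparator rule can change.** Take 99 evaluable per arm and the 9-point margin. All rates are hypothetical.
- Lariam 98%, standard 88%, Cotrifazid 88%. Merged, the comparators average 93%, so Cotrifazid is 5 points below the pool but 10 below Lariam. Non-inferiority is claimed in about 32% of trials against the pool and 4% against Lariam directly. A rule that either comparator suffices succeeds in 62%, and a rule that both must be met in 4%.
- Lariam 95%, standard 86%, Cotrifazid 86%. The pool averages 90.5%, so the gaps are 4.5 and 9 points. The claim is made in about 32% against the pool and 6% against Lariam. That 6% is the nominal 5% with a normal-approximation test.

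**4. Power if both comparisons are required.** All true rates are 95%, with 99 evaluable per arm. SE = √(0.095 / 99) = 0.0310, and 0.09 / 0.0310 − 1.645 = 1.26, giving about 90% per comparison (89% by simulation). Joint power is about 84% by simulation, above the planned 80%.

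**The case against.** The strongest reply is that the protocol already shows which test matters. Section 10.1 has one efficacy hypothesis, 10.3 sizes the trial on it, and failure rate in 5.3.1 is its complement. Nowhere does the protocol say that faster clearance or fewer complications would establish efficacy. In plain English, not inferior to A or B can mean inferior to neither, which keeps the error at or below 5%. Handling of multiplicity is also commonly left to a statistical analysis plan, which may exist.

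Much of this stands, and it rules out two stronger readings.

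- A reader might infer that the protocol plans eight primary tests at 5% each, with an error of about 31%. The text does not support that. The 5% one-tailed level is written only for failure rate and complications, no overall error rate is stated, and three of the outcomes have no margin. The figure is the worst case among several readings.
- A reader might infer that Lariam and standard treatment will be pooled. No section says so. Each arm is sized separately, and the sentence on failure rate speaks of comparator groups. Among the primary tests, only the logrank sentence says two groups. The pooling example shows a risk of the wording and does not describe the plan.

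The inconsistency itself remains. A missing multiplicity method alone would be no finding. A protocol that hypothesises one outcome, labels four as primary and writes two-group tests for three arms has fixed these matters inconsistently in its own text.

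**Conclusion.** The point holds as a mismatch within the protocol: 10.1 and 10.3 on one side, 5.3.1 and 10.4.1.1 on the other, with the comparator rule unstated. Depending on how the gap is filled, one-sided error on the efficacy claim runs from at most 5%, through about 9%, to about 18% to 31%. The first two figures need only the protocol's 5% level and equal arms. The last range also needs the assumed outcome correlations, 5% for the logrank tests, and null hypotheses that the protocol does not state for three outcomes. The 32% pooling figure is conditional on a reading that the protocol does not adopt and on hypothetical rates.

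This should be corrected before analysis. It does not call the design or the number of patients into question.

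**What to change.** - **Sections 5.3.1 and 10.4.1.1 (and the synopsis):** name treatment success (failure rate) as the single primary efficacy endpoint, matching 10.1 and 10.3. Move fever clearance, parasite clearance and complications to secondary.
- **Sections 10.4.1.1 to 10.4.2:** replace the two-group wording by two named comparisons, Cotrifazid versus Lariam and Cotrifazid versus standard treatment, and state that the comparators are not pooled.
- **Section 10.1:** replace or by an explicit rule. Requiring non-inferiority to both, each at one-sided 5%, needs no alpha split.

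A pre-specified fixed order is an alternative. The sponsor would have to choose the order, since nothing in the protocol ranks the comparators. If either comparator is to suffice, one-sided 2.5% each requires 93 evaluable, or 104 per arm after 10% loss, which 110 covers (about 83% power at 99 evaluable).

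The cost is wording, with no extra patients. Three outcomes lose the primary label, and under the both-required rule the claim depends on two comparisons. Keeping all eight tests primary with a Bonferroni split (0.05 / 8 = 0.625%) would instead need 131 evaluable for treatment success alone, or 146 per arm and 3 × 146 = 438 in total.
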